#### Process evaluation

The process evaluation will include an interventionist questionnaire, capturing how many times interventionists have used Social Stories™; and whether they have trained others. Interviews and fidelity assessment will be carried out. A Social Story™ writing and delivery training DVD will be developed and an FAQ document identifying elements of good practice in the implementation of Social Stories™ as well as any common issues or barriers highlighted by interventionists and/or parents. Both of these outputs will be freely available on the research team’s website.

#### Qualitative analysis

Semi-structured interviews will be undertaken with 10–20 participants to explore challenges and barriers to training and implementation of Social Stories™, and the willingness of school staff to run the intervention independently. These participants will be purposively selected from the cohort of teachers, trainers, interventionists, Associated Teachers, local authority representatives involved in the trial and parents who attended the training. With consent, all interviews will be recorded on encrypted devices, transcribed verbatim and anonymised. A sample of data transcripts will be checked against audio recordings for accuracy. Interview material will be organised according to analytical headings using a constant comparison approach [41]. Qualitative data analysis computer software will be used to structure and explore the interview data. Electronic sound files and transcripts from qualitative interviews will be assigned a unique participant number, known only to relevant members of the research team. Any quotes published will be anonymous.

#### Fidelity analysis

The fidelity evaluation will examine the extent to which the components of the intervention (Social Stories™) were delivered as planned, and the accommodations required by schools to ensure this. Interventionists’ adherence to core components will be assessed via researcher completed fidelity checklists of each Social Story™ after initial writing and at 6 weeks.

#### Economic analysis

The economic analysis will be conducted from an NHS and Personal Social (PSS) perspective, taking the form of a within-trial cost-effectiveness analysis determining the incremental cost per unit of outcome effectiveness measure for Social Stories™ compared with care as usual in children with autism. Health outcomes will be measured in terms of quality-adjusted life-years (QALYs) using the EQ-5D-Y (proxy version) as a health descriptor measure (the preferred instrument in the NICE reference case). The domains of the EQ-5D-Y proxy will then be valued using UK population tariff to provide utility scores at multiple time points. QALYs will be estimated using time weighted averages of the utility scores measured over the study time period.

The cost of the Social Stories™ intervention will be calculated using a bottom-up estimation of the time spent by professionals delivering the intervention, the cost of training and other resources used. Unit costs of health service use will be obtained from the UK national database of reference costs. The cost of social services will be calculated from the Unit Costs of Health and Social Care, produced by the Personal Social Services Research Unit, and the cost of other professional support will be estimated from relevant salary scales and published reports/ literature.

A sensitivity analysis will be conducted including costs of productivity loss.

### Data monitoring

The conduct of the study will be governed by three committees.
A Trial Steering Committee (TSC).An independent Data Monitoring and Ethics Committee (DMEC).A Trial Management Group (TMG).

These committees will function in accordance with YTU SOPs. The DMEC and TSC are both independent from the sponsor. The TSC will consist of an independent chair, an independent subject specialist, an independent clinical academic, an independent statistician and a Patient and Public Involvement (PPI) representative. The DMEC will consist of an independent chair, an independent statistician, and another independent member experienced in research with children and families. The TSC and DMEC will meet approximately every 6 months from the start of the trial. The TMG will comprise co-applicants, members of the trial team (including the data manager), PPI representatives, and the trial managers. Co-applicants and trial team members will be invited as required depending on their roles.

### Adverse event reporting

Possible harm as a result of the study will be monitored according to YTU SOPs. Any Adverse Events (AEs) reported by individuals participating in the study will be recorded using a bespoke Adverse Events Recording Form and assessed for seriousness. AEs will be recorded as a Serious Adverse Event (SAE) if it results in death, is life threatening, prolongs or requires hospitalisation, or results in disability or incapacity. Any AEs relating to study participation and all SAEs will be reported to the CI. SAEs related to the study will be reported to the study Sponsor, DMEC and TSC.

The DMEC will review data throughout the trial for safety. If there is evidence of harm due to the intervention or measures used, the DMEC will advise the TSC with a possible recommendation to stop the trial.

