#### Secondary

The secondary objectives of this trial are:
To investigate whether Social Stories™ can reduce challenging behaviour in children with ASC in primary schools.To investigate whether Social Stories™ can improve social and emotional health in children with ASC in primary schools.To assess the cost-effectiveness of Social Stories™.To examine the effects of Social Stories™ delivered in the classroom on general measures of health related quality of life.To examine whether Social Stories™ improve classroom attendance.To assess sustainability of Social Stories™ in an education setting across a 6 month period.To examine any changes in parental stress.To examine any associations between treatment preference and outcomes.To examine how elements of session delivery (e.g. session frequency, length and any associated problems/adverse events) are associated with outcomes.

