**Fig. 1 Fig1:**
[figure not shown]
Study Flow Chart

Parent questionnaires:
Social Responsiveness Scale, Second Edition (SRS-2) [34].Demographic information pertaining to the child and the parent – *baseline only.*Parenting Stress Index short form [35].The EQ-5D-Y (proxy) [36].Revised Children Anxiety and Depression Scale (RCADS) short form [37].Bespoke resource use questionnaire, capturing healthcare and non-health resource use of participants and parents/carers– *baseline and 6 months only.*Bespoke treatment preference questionnaire – *baseline only.*

Associated teacher/TA questionnaires:
Social Responsiveness Scale, Second Edition (SRS-2) [34].A goal-based outcome measure (adapted from the Child Outcomes Research Consortium) [38].Bespoke resource use questionnaire – *baseline and 6 months only.*Bespoke treatment preference questionnaire – *baseline only.*Bespoke resource use questionnaire determining current school care/education plan interventions – *baseline and 6 months only.*

Interventionist Teacher/ TA Questionnaires:
Bespoke Social Story™ session log. – *used after each Social Story™ session.*A bespoke sustainability questionnaire – *6 weeks and 6 months only.*

Process Evaluation - Researcher Questionnaires:
A fidelity checklist (intervention arm only) assessing each Social Story™ - *after the story has been created and at 6 weeks post-randomisation*.A goal-based measure – used when observing randomised children at 6 weeks and 6 months.

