#### Primary and secondary outcomes analysis

The primary analysis will compare teacher reported SRS-2 t-scores measured at 6 months between the randomised groups using a covariance pattern mixed model. Important baseline covariates, baseline SRS-2 t-score, the SEN status of the child’s school (SEN vs. non-SEN), the number of recruited children in the child’s school (> 5 vs. ≤5), time point, treatment group, and a treatment group-by-time point interaction will be included as fixed effects and school will be included as a random effect. SRS-2 t-scores at 6 weeks post randomisation will be incorporated as outcome data. The model will account for the correlation of scores within pupil over time by means of an appropriate covariance structure. Intervention effects in the form of an adjusted mean difference will be presented with an associated 95% CI and *p*-value for both time points (6 weeks and 6 months).

Secondary outcomes will be analysed in a similar manner to the primary analysis, adjusting for the appropriate baseline score being tested. The summary of Adverse Events (AEs) and Serious Adverse Events (SAEs) experienced by participants will be reported by treatment group.

Subgroup analyses will be performed to explore the potential effect of teacher’s preferred randomisation group collected at baseline. The primary analysis model will be refitted with an interaction term between the randomisation group and teacher’s preference. A Complier Average Causal Effect analysis for the primary outcome will be considered to account for compliance with the intervention at the student level.

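### Non-serious adverse events are summarised by arm, but session-level capture is possible only in the intervention arm

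*Protocol article*

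**What the plan says.** The protocol article deals with harms in four places.

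- **Adverse event reporting.** "Possible harm as a result of the study will be monitored according to YTU SOPs". The entry route is then given: "Any Adverse Events (AEs) reported by individuals participating in the study will be recorded using a bespoke Adverse Events Recording Form", and each event is judged serious or not. The section makes no distinction by arm. Serious events (SAEs) are defined by a short list of outcomes such as death and hospitalisation.
- **Primary and secondary outcomes analysis.** "The summary of Adverse Events (AEs) and Serious Adverse Events (SAEs) experienced by participants will be reported by treatment group". No test or effect estimate is planned for these events.
- **Study objectives, Secondary.** One objective is to relate elements of session delivery to outcomes. The elements named are "session frequency, length and any associated problems/adverse events".
- **Outcomes (primary and secondary).** The interventionist's instruments include a bespoke session log, "used after each Social Story" session. The instruments listed for parents and associated teachers, who serve both arms, include none identified as an AE enquiry.

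Under Intervention, interventionists are placed in schools allocated to the intervention. Under Control, the other schools are asked not to use Social Stories. Under Blinding, families and school staff are unblinded. Under Data collection, the contacts at baseline, 6 weeks and 6 months are given without any difference by arm.

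**The concern.** A by-arm harms table can be read as a comparison only if an event of the same kind has the same chance of being recorded in each arm. Here one arm has an additional member of staff, unblinded, who writes a record after every session. The plan expects adverse events to be noted at that level. The other arm has neither the person nor the record.

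Minor events are the ones most affected by how often someone is asked to write something down. The eligibility criteria require daily challenging behaviour, so minor incidents may well be frequent. If events seen only through the session route enter the by-arm summary, a harmless intervention could appear to produce more of them. The published safety table would carry that distortion. So would the DMEC's safety review, if it is shown by-arm AE counts.

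**Working it through.** The article states no AE rate or capture rate, so there is no figure of the plan's to reproduce. The check sets its statements side by side.

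1. **Who can put an event on the record?** Any participating individual (Adverse event reporting). The Recruitment section counts about 140 interventionists among those recruited, so an event reported by an interventionist qualifies.
2. **Is session-level capture of adverse events intended?** Yes. The secondary objective on session delivery cannot be addressed unless session-associated events are recorded somewhere.
3. **Where are they recorded?** The only session-level instrument listed is the session log. That it holds these events is an inference, though the most plausible one.
4. **Does the control arm have an equivalent?** No. Interventionists and sessions belong to intervention schools (Intervention, Control). The observation of 20% of children by research assistants is likewise drawn only from the intervention arm.
5. **Are the reporters blinded?** No (Blinding).
6. **Is there a rule separating these events from the by-arm summary?** None is stated. The summary covers AEs and SAEs "experienced by participants will be reported by treatment group".

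**Would an identical AE question at the common contacts be enough?** Suppose the true risk *p* is the same in both arms and the common contacts capture a fraction *a* of events in each. Suppose also that the session route captures a fraction *b* of the events the contacts miss.

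- Control, recorded risk: *p* × *a*
- Intervention, recorded risk: *p* × [*a* + (1 − *a*) × *b*]
- Apparent risk ratio: [*a* + (1 − *a*) × *b*] / *a* = 1 + *b* × (1 − *a*) / *a*

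The ratio equals 1 only if *b* = 0 (no log-only events enter the table) or *a* = 1 (the common contacts miss nothing). A common question can raise *a* but does not make *b* zero. The tabulation rule does that.

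The article gives none of *p*, *a* and *b*, so the expression shows the mechanism and not its size. It also assumes that *a* is equal in the two arms. With unblinded reporters it may not be, and that could move the ratio either way.

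**The case against.** The strongest reply is that much of this rests on silence in a condensed article. The log's contents are not given. No sentence says that log entries reach the AE form or the by-arm summary. The one named route, the AE form, is open to both arms. Harm monitoring is deferred to trials unit procedures that are not shown, and these may require an AE question at 6 weeks and 6 months. Parents in both arms also complete a resource-use questionnaire covering healthcare. The planned summary is descriptive and claims no equal capture. A DMEC recommendation to stop depends on evidence of harm due to the intervention or measures, which is a judgement of attribution and not a comparison of raw counts.

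Most of this stands, and it rules out three stronger readings that a reader might reach.

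- *AE collection is purely spontaneous.* The article says that individuals report events. It does not say whether they are asked, and the absence of a scheduled question here is not a finding.
- *The comparison is biased by design.* That would require log entries to be known to feed the table. The article leaves this open.
- *The imbalance can be quantified.* With an equal split, 278 / 2 = 139 children per arm, and a minimum of six sessions each gives 139 × 6 = 834 log entries, against none in control. Those are sessions, not AE enquiries, and a control count of zero presumes questionnaire content that is not shown. Any ratio built on assumed capture percentages only returns the assumption.

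The reply does not remove the structural point. Even if the unshown procedures ask about AEs identically at the common contacts, the intervention arm keeps its extra session-level route, and the article states no rule for events known only through it.

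**Conclusion.** The concern holds as a risk of differential ascertainment of non-serious AEs. It rests on three things the article states: participants' AE reports are recorded without restriction, AEs are summarised by arm, and session-level contact with unblinded interventionists exists in one arm only. It also rests on one inference, that session-associated adverse events are noted in the session log.

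The size of any bias cannot be determined from the article, nor whether it occurs in practice. SAEs are less exposed because their criteria are fixed and the same in both arms. The point is worth acting on because the remedy is nearly free and determines what the by-arm table shows.

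**What to change.** State in the analysis plan that the by-arm AE table, and any by-arm AE counts given to the DMEC, use only events collected the same way in both arms. In practice these are events from the common 6-week and 6-month contacts. If the questionnaires or trials unit procedures do not already ask about AEs there, add an identical question in both arms.

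Tabulate events known only from session logs or from intervention-arm observation separately, as descriptive intervention-arm data without comparison. Continue to report all SAEs, whatever their source.

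The cost is a split safety table. If the common question already exists, a clarifying sentence is enough. If an item has to be added, note that recruitment opened in November 2018: earlier and later participants would then be ascertained differently, though equally in both arms.

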### Protocol amendments

Prior to submission for ethical approval, protocol amendments will be approved by the CI, substantial amendments will be approved by the CI, Sponsor and TMG. Amendment history will be tracked by adopting version control and by the use of an amendment log.

### Dissemination

Results will be published in mainstream and specialist science journals. Study findings will be presented at relevant research conferences, symposia and seminars. In addition, the National Autistic Society and members of service user groups such as ASCEND will be consulted in the development of methods for dissemination that will be effective in reaching families of children with ASC. We will also produce a short summary of results that can be distributed to trial participants as well as relevant interest and patient groups. We will publish findings on relevant websites such as the National Autistic Society, university and child mental health websites. We aim to ensure coverage of our findings in the wider media by issuing a press release.

Towards the end of the trial, our PPI representatives will organise a meeting with stakeholders including parents and professionals working with young people who have ASC to discuss the dissemination of the study findings. We will hold a research dissemination event for national and local clinicians and policy makers. Depending on findings, we will make suggestions to NICE about treatment evidence.

## Discussion

This study aims to examine the clinical and cost effectiveness of Social Stories™ intervention when used in education settings with primary school children. This large scale trial builds upon the initial feasibility work conducted [32], and will enhance a growing body of promising literature [15, 18–31] by comparing the outcomes of children receiving care as usual only and children receiving Social Stories™ in addition to care as usual in a fully powered RCT. Results from this study will help to inform school based interventions for children with a diagnosis of ASC.

### Study limitations

Due to the nature of the intervention it is not possible for participants to be blinded to study allocation, however the trial research assistants well as the trial statistician remain blinded to help mitigate any potential impacts. Further this study focusses solely on the use of Social Stories™ in education based settings, dependent on study findings, further randomised research into the use of Social Stories™ in the home may prove beneficial.

## Data Availability

Anonymised participant data from the ASSSIST2 trial will be made available via the sponsor. Those wishing to access this data must apply to the sponsor and show that they have sound scientific reasons for requesting access to the data as well as having acceptable research methods. Other documents that will be made available include the study’s protocol, statistical analysis plan, health economics plan as well as the case report forms used throughout the study. This data will become available following publication.

## Abbreviations

AEs: Adverse Events
ASC: Autism Spectrum Conditions
ASCEND: Autism Spectrum Conditions – Enhancing Nurture and Development
ASSSIST2: Autism Spectrum Social Stories In Schools Trial 2
CACE: Complier Average Causal Effect
CI: Chief Investigator
CONSORT: Consolidated Standards of Reporting Trials
CRFs: Case Report Forms
DMEC: Data Monitoring and Ethics Committee
EOI: Expression of Interest
HRA: Health Research Authority
ISRCTN: International Standardised Randomised Controlled Trial Number
ITT: Intention to treat
NICE: The National Institute for Health and Care Excellence
NIHR: National Institute of Health
PPI: Patient and Public Involvement
PSS: Personal Social
QALYs: Quality Adjusted Life Years
RCADS: Revised Children Anxiety and Depression Scale
RCT(s): Randomised Controlled Trial(s)
SAEs: Serious Adverse Events
SEN: Special Educational Needs
SENCO: Special Educational Needs Coordinator
SOPs: Standard Operating Procedures
SRS-2: Social Responsiveness Scale Second Edition
TA: Teaching Assistant
TMG: Trial Management Group
TSC: Trial Steering Committee
YTU: York Trials Unit
